### Randomization

All women with risk of PPD that meet the inclusion criteria and none of the exclusion criteria will be randomized with Random Allocation Software. For this purpose, all the groups from the participating hospitals will send the initials of each patient recruited to the study coordinator who will specify the allocation of the patient (to the control or intervention group); the person in charge of the assessments will be blind to this process.

### Patient assessment

Data on the wide range of clinical and demographic variables detailed below will be gathered using a data collection form. All candidate women will be assessed in the third trimester of pregnancy in order to screen for the presence of any of the aforementioned risk factors. Scales to assess socioeconomic status and personality vulnerability will also be administered in this screening. The next assessment will be the baseline assessment of all the women that are found to have at least one risk factor for PPD in the screening between 8 and 15 days after the childbirth. At this point, we will assess the mother’s physical activity and child’s temperament and measure the depressed mood of the mother with the EPDS. Women scoring ≥ 7.5 who are then then randomized to one of the two groups (control vs experimental) will be assessed weekly until the completion of six psychoeducational sessions, nearly 2 months after the baseline assessment. The control groups will be also re-assessed after the same interval.

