## Methods/Design

We registered this single-blind randomized clinical trial in 2014 (identifier NCT02323152). Women will be recruited in the third trimester of pregnancy from 2015 to the completion of the study. Women that agree to participate and sign the informed consent form will then be assessed through a first screening visit by their reference midwife; specifically, the midwife will record sociodemographic data and the presence of various previously described risk factors, including the personality vulnerability of the woman and her socioeconomic status.

Women with at least one risk factor will progress to the next phase of the study and will be assessed between 8 and 15 days after the birth of their baby, at the Araba University Hospital. Clinical data will be collected relating to the delivery. We will also evaluate the women’s mood with the Edinburgh Postnatal Depression Scale (EPDS) [22], the child’s temperament with the Merrill-Palmer-Revised Scales of Development [23] and the current and overall physical activity of women with the International Physical Activity Questionnaire (IPAQ) [24] and Global Physical Activity Questionnaire (GPAQ) [25] using the Spanish versions of these tools. A score between 7.5 and 12.5 on the EPDS indicates depression risk and women with scores in this range will progress to the next phase of the study. In this phase, the participants will be randomized with Random Allocation Software 1:1 to the experimental or control group (treatment as usual). Women in the experimental group will receive six (1 individual and 5 group) sessions of the psychoeducational intervention and their status will be evaluated weekly. The control group will continue to have regular appointments with the midwife and gynaecologist and will be assessed again 6 weeks after inclusion in the trial.

We will recruit patients from five health centres in Vitoria and two health centres in Donostia, and the study is being coordinated by the Psychiatry Research team of Araba University Hospital, which is a member of the Center for Biomedical Research Mental Health Network (CIBERSAM). Patients meeting all the inclusion criteria and none of the exclusion criteria (listed below) will be included in the study.

The trial will be conducted in accordance with good clinical research practice, enabling the research to be carried out with low risk of bias and a high degree of external validity.

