### Exclusion criteria

Mental retardationWorsening of a severe mental disorder that could hinder understanding of the objectives of the studyLanguage difficulties that impede verbal comprehension, reading and/or writingPresence of a major depressive episode according to the DSM-IV-TR (depressive symptoms of sufficient intensity and duration longer than 2 weeks).

All participants will be informed that they will be randomized to one of the two study groups and will only be included if they give their informed consent to participate in the study. Women in both groups will be assessed at baseline (pre-intervention) and 6 weeks (post-intervention).

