### Intervention programme

Our Postpartum Depression Prevention Programme (PDPP) consists of six 1-h weekly sessions, for 2 months, focused on improving the information that the women have about depression syndrome, patient insight into their illness, early intervention for prevention, healthy lifestyles, techniques for managing anxiety, social skills and problem solving.

The first session is individual, and the remaining ones are group sessions. The programme has an open format. That is, each woman that is randomized to the experimental group will directly enter the group, and start receiving the intervention, regardless of the session number. The rationale behind this is that women should not have to wait until a group is formed. In this way, we minimize the risk of the symptoms worsening.

The programme includes the following sessions:What is PPD? Etiological and trigger factorsRisk Factors for PPDHow to manage negative thoughtsTechniques for reducing stress and anxietyProblem-solving techniquesHealthy lifestyle and technical guidance on seeking practical solutions

The psychoeducational sessions will only be run in Araba University Hospital. Further, the therapists will have a specific training to give the psychoeducational intervention to all women in the same way, and provide the same information, enhancing the reliability of the study.

Lastly, if participants have any question about the sessions, or about their condition, they will be able to call a telephone helpline in working hours (between 08.00 and 15.00 from Monday to Friday). The aim of this service is to facilitate participants’ access to information and address any questions they might have.

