### Data processing

Comparisons of baseline characteristics of the sample will be made with χ2-tests for categorical variables and the Student’s t-test or Mann Whitney U test for quantitative variables, depending on the distribution of the data. Differences in mood symptomatology during treatment will be examined using Wilcoxon signed-rank test for the within-group analyses and the Mann–Whitney U test for the between group analyses. The latter will also be used to analyse variation in EPDS scores between groups. On the other hand, cut-off points for the EPDS will be established and differences in the categorical variables created will be analysed with χ2-tests. Linear regression models will be performed for each group to evaluate the influence of the child’s temperament and global and daily activity during treatment on mood symptoms.

Univariate analyses of covariance will be conducted to investigate differences between groups. For this, the independent variable will be the group assignment (treatment as usual plus psychoeducation treatment versus treatment as usual alone) and the dependent variables will be the respective clinical or functional outcome scores post-treatment. This analysis will be performed on an intention-to-treat basis, with women being analysed in the treatment group to which they were randomized. In addition, a logistic regression model will be used to assess the relationships between clinical variables.

Finally, we will also build an ordinal regression model to explore factors associated with having depression after the intervention. The categorical variable of the EPDS assessed post-intervention will be used as the dependent variable, while risk factors evaluated at baseline will be the independent variables.

The outcomes will be reported with 95% confidence intervals. All data will be analysed using IBM SPSS Statistics v22.

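### The post-intervention EPDS is timed at 6 weeks in two sections and at session completion, just under two months, in another, so the arms could be measured about 2 to 3 weeks apart

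*Protocol article*

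**What the plan says.** Four sections of the protocol article bear on when the post-intervention EPDS is taken.

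- **Methods/Design.** The baseline EPDS belongs to a visit at which women "will be assessed between 8 and 15 days after the birth of their baby". After randomisation, the control group "will be assessed again 6 weeks after inclusion in the trial". For the experimental group the section says only that "their status will be evaluated weekly"; it gives no date for the last assessment.
- **Exclusion criteria** (closing paragraph). "Women in both groups will be assessed at baseline (pre-intervention) and 6 weeks (post-intervention"). No starting point is named for the 6 weeks.
- **Patient assessment.** Randomised women "will be assessed weekly until the completion of six psychoeducational sessions, nearly 2 months after the baseline assessment". The next sentence adds: "The control groups will be also re-assessed after the same interval".
- **Intervention programme.** The programme "consists of six 1-h weekly sessions, for 2 months".

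The score is then used under Data processing. In the analysis of covariance between the arms, "the dependent variables will be the respective clinical or functional outcome scores post-treatment", and that analysis is by intention to treat.

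**The concern.** The time of the outcome visit is part of the definition of the outcome. Here it has two values, two starting points (inclusion and the baseline assessment) and two kinds of end point (a calendar date and an event, the completion of six sessions).

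The event is the weaker choice. When a woman reaches her sixth session depends on how she attends. Sessions are held only at the coordinating hospital in Vitoria, while two of the recruiting centres are in Donostia, so uneven attendance is plausible. A woman who never reaches six sessions has no assessment time under that rule, and a control woman has no sessions to complete. An intention-to-treat comparison needs an outcome time that exists for every randomised woman and means the same thing in both arms.

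If staff took the control date from one section and the experimental date from another, the difference between arms would mix the effect of the programme with any change in EPDS over the extra days.

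**Working it through.** There is no figure of the plan's own to reproduce on this point, so the check is calendar arithmetic and a comparison of the sections.

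**Inputs**

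| Item | Value | Source |
|---|---|---|
| Control visit | 6 weeks from inclusion | Methods/Design |
| Both arms | 6 weeks, origin not named | Exclusion criteria |
| Randomised women; controls at the same interval | six sessions completed, just under two months from baseline | Patient assessment |
| Programme length | six weekly sessions, yet two months | Intervention programme |
| Baseline | 8 to 15 days after birth | Methods/Design |
| Just under two months, in days | 56 to 61 | assumption |

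**Step 1: are the two times the same visit?** 6 weeks = 6 × 7 = 42 days. The gap is 56 − 42 = 14 days to 61 − 42 = 19 days, that is 2.0 to 2.7 weeks, or 33% to 45% of the 6-week interval.

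**Step 2: where do they fall after birth, if both count from baseline?** At 6 weeks: 8 + 42 = day 50 to 15 + 42 = day 57. At 56 to 61 days: 8 + 56 = day 64 to 15 + 61 = day 76. The ranges do not overlap.

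**Step 3: does the difference in origin explain the gap?** If inclusion follows baseline by L days, the control visit falls on day 42 + L from baseline, and the gap becomes 14 − L to 19 − L days. A lag shortens the gap and would have to reach 14 to 19 days to close it. The article gives no value for L.

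**Step 4: does the programme schedule settle it?** Six sessions at weekly spacing run 5 × 7 = 35 days from first to last. To reach 56 to 61 days from baseline, a further 21 to 26 days must come from a wait before the first session or from weeks without one. The article does not say which. The completion date therefore contains 3 weeks or more that are not accounted for and could differ between women.

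**Step 5: what would a gap do to the comparison?** Shift in the between-arm difference = change in EPDS per week × gap in weeks. The weekly change is not in the article, so these values are purely illustrative, and the sign is open:

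| Assumed change per week (either direction) | Shift for 2.0 to 2.7 weeks | Share of the 5.5-point target difference |
|---|---|---|
| 0 | 0 | 0% |
| 0.1 | 0.20 to 0.27 points | 3.6% to 4.9% |
| 0.25 | 0.50 to 0.68 points | 9.1% to 12.3% |
| 0.5 | 1.00 to 1.35 points | 18.2% to 24.5% |

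**The case against.** The strongest reply is that the plan intends equal timing and says so twice. The sentence under Exclusion criteria gives both arms the same 6 weeks, and Patient assessment gives controls the same interval as the experimental arm. A gap arises only by taking the control date from Methods/Design and the experimental date from Patient assessment, and the latter section itself rules that combination out. This stands as a statement of intent. It does not settle what the interval is: the one exact time given for a control is 6 weeks, and the interval she is meant to share ends with an event she does not have.

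Three stronger readings are tempting and should not be drawn.

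- *The plan measures the arms at different times.* It does not prescribe this. Unequal timing is a risk created by text that conflicts.
- *Any bias would favour the programme, because women selected for raised scores soon after birth improve with time.* No section gives a trend in the EPDS. The Intervention programme section even justifies open groups by the risk that symptoms get worse while women wait. If untreated women worsened, measuring controls earlier would count against the programme. Regression to the mean after selection affects both arms on re-measurement and need not build up week by week.
- *Women who stop attending are lost from the experimental arm only.* Nothing says so. Weekly evaluations are planned and analysis is by randomised group. An article may also leave the follow-up of non-attenders to the full protocol or analysis plan.

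The reply about origins also has force: inclusion may come some days after baseline, so 14 to 19 days is an upper range.

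**Conclusion.** The concern holds as an internal contradiction about when the compared outcome is measured. The two stated times differ by 14 to 19 days if just under two months is 56 to 61 days and both are counted from the same origin, and by less if inclusion follows baseline with a lag. Tying one of them to session completion makes the time dependent on attendance and leaves it undefined for controls. The arms could therefore be measured roughly 2 to 3 weeks apart, although the authors plainly want them measured together. The size and direction of any bias are unknown, since they depend on a weekly change in EPDS that the article does not give; the shifts tabulated above are illustrations, and at zero change there is none. The point needs correcting all the same, because a single fixed time removes the risk at almost no cost and gives the intention-to-treat comparison an outcome time that applies to every randomised woman.

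**What to change.** 1. State one post-intervention assessment time, counted from randomisation, with one visit window, identical in both arms and independent of the number of sessions attended.
2. Assess every randomised woman at that time, including those who have stopped attending.
3. Name the EPDS from that visit as the score in the post-treatment between-group comparison. The analyses of mood during treatment can stay as they are.
4. Bring Methods/Design, Exclusion criteria, Patient assessment and Intervention programme into line with it. The wording on six weekly sessions and two months must be reconciled as well; which session schedule applies is for the investigators to state.

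The change is one of wording and adds no visit. Its one drawback is that some women in the experimental arm may be assessed before their last session. Their score would then reflect the programme as delivered up to the common time, which is compatible with analysis by randomised group.

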### Demographic and other personal data

We will collect data on age, sex, ethnicity, level of education, living arrangements, employment status, problems in the delivery and medication use (in such cases).

### Risk factors

We have compiled a list of risk factors (RF) associated with PPD based on an electronic search in PubMed. The midwife will note if the pregnant women have any of these factors.

Specifically, we included the following RFs as the most closely related to PPD:Depressive or anxious pathology during pregnancyPersonal history of severe mental disorder (schizophrenia and other psychoses, bipolar disorder, depressive disorder)Family history of severe mental disorderConcomitant medical diseases associated with depression (diabetes, heart disease, hypertension, obesity)Low or very low socioeconomic statusLack of support for women (partner, family, friends or others).

### Mood assessment

The **EPDS** will be used to assess participants’ depressive symptoms [22]. This 10-item self-report tool is designed to screen women for symptoms of emotional distress during pregnancy and the postnatal period.

### Vulnerable personality assessment

The Vulnerable Personality Style Questionnaire **(VPSQ)** is a nine-item self-report scale developed to assess personality traits which increase the risk of PPD [13].

### Physical Activity Questionnaires

The **IPAQ** provides a set of well-developed instruments that can be used internationally to obtain comparable estimates of physical activity. The long version we will use provides the detailed information often required in research work or for evaluation purposes [24].

The **GPAQ** was developed by WHO for monitoring physical activity [25]. It collects information about participation in physical activity and sedentary behaviour in three domains:Activity at workActivity related to traveling to and from placesLeisure activities

### Children’s temperament style

**MP-R:** We will measure the child’s temperament with the Merrill-Palmer–Revised Scales of Development [23]. This instrument evaluates five main areas of development: cognition, language and communication, motor skills, adaptive behaviour, and socioemotional domains. It provides information about global development of the child to assess the presence of possible delays in some areas.

All the instruments to be used have demonstrated adequate psychometric properties and have been used in many other studies. Interviews will be conducted by clinicians who have good inter-rater reliability for the scales used.

### Intervention programme

Our Postpartum Depression Prevention Programme (PDPP) consists of six 1-h weekly sessions, for 2 months, focused on improving the information that the women have about depression syndrome, patient insight into their illness, early intervention for prevention, healthy lifestyles, techniques for managing anxiety, social skills and problem solving.

The first session is individual, and the remaining ones are group sessions. The programme has an open format. That is, each woman that is randomized to the experimental group will directly enter the group, and start receiving the intervention, regardless of the session number. The rationale behind this is that women should not have to wait until a group is formed. In this way, we minimize the risk of the symptoms worsening.

The programme includes the following sessions:What is PPD? Etiological and trigger factorsRisk Factors for PPDHow to manage negative thoughtsTechniques for reducing stress and anxietyProblem-solving techniquesHealthy lifestyle and technical guidance on seeking practical solutions

The psychoeducational sessions will only be run in Araba University Hospital. Further, the therapists will have a specific training to give the psychoeducational intervention to all women in the same way, and provide the same information, enhancing the reliability of the study.

Lastly, if participants have any question about the sessions, or about their condition, they will be able to call a telephone helpline in working hours (between 08.00 and 15.00 from Monday to Friday). The aim of this service is to facilitate participants’ access to information and address any questions they might have.

### Treatment as usual

Treatment as usual refers to the treatment that is routinely provided to pregnant women in the Spanish National Health Service. It consists of ambulatory appointments with their midwives and gynaecologist. They will not receive any therapeutic input from the psychologist.

### Expected timetable for the study

Figure 1 shows the flow of women though in the study.

**Fig. 1 Fig1:**
[figure not shown]
CONSORT diagram. The CONSORT diagram illustrates and reports the progression of the participants through the different points of the study

### Data processing

Comparisons of baseline characteristics of the sample will be made with χ2-tests for categorical variables and the Student’s t-test or Mann Whitney U test for quantitative variables, depending on the distribution of the data. Differences in mood symptomatology during treatment will be examined using Wilcoxon signed-rank test for the within-group analyses and the Mann–Whitney U test for the between group analyses. The latter will also be used to analyse variation in EPDS scores between groups. On the other hand, cut-off points for the EPDS will be established and differences in the categorical variables created will be analysed with χ2-tests. Linear regression models will be performed for each group to evaluate the influence of the child’s temperament and global and daily activity during treatment on mood symptoms.

Univariate analyses of covariance will be conducted to investigate differences between groups. For this, the independent variable will be the group assignment (treatment as usual plus psychoeducation treatment versus treatment as usual alone) and the dependent variables will be the respective clinical or functional outcome scores post-treatment. This analysis will be performed on an intention-to-treat basis, with women being analysed in the treatment group to which they were randomized. In addition, a logistic regression model will be used to assess the relationships between clinical variables.

Finally, we will also build an ordinal regression model to explore factors associated with having depression after the intervention. The categorical variable of the EPDS assessed post-intervention will be used as the dependent variable, while risk factors evaluated at baseline will be the independent variables.

The outcomes will be reported with 95% confidence intervals. All data will be analysed using IBM SPSS Statistics v22.

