### Sample size

After a thorough review of the literature and using the Ene 2.0 [27] software, we calculated that for a statistical power of 90%, with a significance level of 5%, a sample of 30 patients per group will allow us to detect mean differences of 5.5 points on the EPDS between the experimental group and the control group (alpha = 0.05, beta = 0.10, *N* = 126). To achieve this sample, 600 participants in the third trimester of pregnancy will be screened for eligibility. Of the total, about 280 are expected to have at least one risk factor and will progress to the second phase of the study. Of these, we estimate that a quarter of the women will score 7.5 or higher on the EPDS, which would leave approximately 60 women to be randomized to the two arms of the trial.

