## Abbreviations

CBT: Cognitive Behavior therapy
EPDS: Edinburgh Postnatal Depression Scale
GPAQ: The Global Physical Activity Questionnaire
IPAQ: The International Physical Activity Questionnaire
MP-R: Merrill-Palmer-Revised Scales of Development
PDHR: Postpartum Depression High Risk
PDPP: Postpartum Depression Prevention Programme
PDVHR: Postpartum Depression Very High Risk
RF: Risk Factor
SE: Socio Economic
TAU: Treatment As Usual
VPSQ: The Vulnerable Personality Style Questionnaire

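### The between-arm chi-square test of the EPDS categories ignores an order that the plan itself recognises; with three or more bands this costs power, though only in a supplementary analysis

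*Protocol article*

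**What the plan says.** All the relevant analysis text is in the Data processing section of the protocol article.

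- **EPDS categories, between arms:** "cut-off points for the EPDS will be established and differences in the categorical variables created will be analysed with χ2-tests".
- **EPDS category as an outcome:** "we will also build an ordinal regression model to explore factors associated with having depression after the intervention". The dependent variable is the post-intervention EPDS category. The independent variables are the baseline risk factors; treatment arm is not among them.
- **EPDS score, between arms:** a Mann–Whitney U test, and analysis of covariance of post-treatment scores by randomised group under intention to treat.
- **Logistic regression:** listed separately, for relations among clinical variables, again without arm.
- **Estimation:** a general commitment to 95% confidence intervals for the outcomes.

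The Sample size section rests on a mean difference in the EPDS score: "a sample of 30 patients per group will allow us to detect mean differences of 5.5 points on the EPDS". It gives no power for any comparison of categories.

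**The concern.** The plan treats one variable in two ways. When related to baseline risk factors, the EPDS category is ordinal. When the arms are compared, it is a set of unordered labels. An ordinal model is of use mainly for three or more levels, and logistic regression is named separately, so the natural reading is that the category has at least three.

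With k bands and two arms, the Pearson test has k − 1 degrees of freedom, and its value does not change if the bands are put in a different order. Two things follow. A consistent shift towards lower bands is spread over several degrees of freedom, which costs power. And a significant result has no direction: it could arise because women moved to both extremes, so by itself it would not show that the programme moved women to lower bands.

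The trial's aim is to prevent postpartum depression, and the plan links this category to having depression after the intervention. It is therefore worth having a comparison that uses the order and yields an estimate.

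**Working it through.** **Inputs from the article**

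- Power and alpha: "for a statistical power of 90%, with a significance level of 5" per cent. Sidedness is not stated; two-sided is assumed.
- Size and effect: 30 per group and 5.5 EPDS points (Sample size).
- Allocation: "randomized with Random Allocation Software 1:1 to the experimental or control group".
- Expected numbers: "which would leave approximately 60 women to be randomized to the two arms of the trial".
- Not given: an SD, and the number and position of the outcome cut-offs.

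**The plan's own figure.** Without an SD, 30 per group cannot be reproduced; it can only be solved for the SD it needs:

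SD = 5.5 / [√(2/30) × (1.960 + 1.282)] = 5.5 / (0.2582 × 3.2415) ≈ 6.57 (6.46 with the t distribution).

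The same sentence also gives "alpha = 0.05, beta = 0.10, *N* = 126". At 63 per group that needs SD = 5.5 / [√(2/63) × 3.2415] ≈ 9.52, so both figures cannot rest on one SD. That is a separate matter. I use 30 per arm because it agrees with the expected 60 women.

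**Step 1: theory.** For the same noncentrality, power at two-sided 5% falls as degrees of freedom rise. For example, 80% power on 1 df corresponds to a noncentrality of (1.960 + 0.842)² ≈ 7.85.

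| 1 df | 2 df (three bands) | 3 df (four bands) |
|---|---|---|
| 90% | 83.5% | 78.4% |
| 80% | 70.9% | 64.5% |
| 70% | 59.7% | 53.1% |
| 60% | 49.5% | 43.2% |
| 50% | 40.1% | 34.5% |

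The loss is 6.5 to 10.5 points on 2 df and 11.6 to 16.9 on 3 df.

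**Step 2: simulated tables under proportional odds.** There are 30 per arm and 20,000 runs per scenario. Pearson chi-square is compared with the tie-corrected Mann–Whitney test on the same bands. The odds ratio (OR) multiplies the control odds of being at or below each cut. Example: control thirds have cumulative odds 0.5 and 2. With OR 3 these become 1.5 and 6, so the cumulative shares are 0.60 and 0.857 and the bands hold 0.60, 0.26 and 0.14.

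| Control shares (assumed) | OR | Chi-square | Order-using | Loss (points) |
|---|---|---|---|---|
| thirds | 2 | 23.0% | 30.0% | 7.0 |
| thirds | 3 | 50.4% | 61.1% | 10.7 |
| thirds | 4 | 69.8% | 79.6% | 9.8 |
| 0.5 / 0.3 / 0.2 | 2 | 20.4% | 26.9% | 6.5 |
| 0.5 / 0.3 / 0.2 | 4 | 59.9% | 70.9% | 11.0 |
| quarters | 2 | 20.2% | 31.5% | 11.3 |
| quarters | 3 | 45.9% | 63.4% | 17.5 |
| 0.4 / 0.3 / 0.2 / 0.1 | 3 | 40.3% | 59.2% | 18.9 |
| halves | 3 | 51.7% | 51.7% | 0 |

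At OR 1 both tests reject in 4.5% to 5.2% of runs, so the gain is not bought with type I error.

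**Step 3: simulated scores cut at 7.5 and 12.5.** These are the limits of the risk range in Methods/Design, borrowed here as assumed outcome cut-offs. SD is 6.57 and the shift 5.5 points.

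| Control mean (assumed) | Chi-square, 3 bands | Order-using, 3 bands | Mann–Whitney, full score |
|---|---|---|---|
| 9 | 66.5% | 76.7% | 86.0% |
| 11 | 70.6% | 80.3% | 87.2% |
| 13 | 71.5% | 80.6% | 87.5% |

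The loss on the bands is 9 to 10 points. A further simulation had scores rounded and kept within 0 to 30, SD 6.46, control means 7 to 11 and a 1-df linear-by-linear trend test. It gave 62–71% against 73–81%. With SD 4 to 5 and the same standardised effect it gave 58–74% against 71–83%; with SD 4 and a shift of 2.5 points, 35–46% against 48–57%. The largest gaps in these scenarios are about 13 points.

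**The case against.** The strongest reply is that the plan already has better between-arm tests. Mann–Whitney on the full score and ANCOVA both use order and show direction, and ANCOVA gives a mean difference. In the step 3 scenarios Mann–Whitney on the score has 86–88% power, more than the trend test on the bands. This stands, and it limits the point to a supplementary analysis. A reader might infer that the trial as a whole loses power, or that this is its only comparison of the arms on the EPDS. Neither is supported, and the sample size itself is set on the score.

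A second reply is that the category may have only two levels. The text speaks of categorical variables in the plural, which could mean several two-way splits, and for those chi-square loses nothing. This stands as a condition. Still, an ordinal regression on the variable fits a two-level reading poorly.

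Three further inferences go too far:

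- **A fixed loss.** No single figure follows from the article, because cut-offs, SD and effect on the bands are all assumed. The values 7.5 and 12.5 appear there for eligibility, not as outcome bands.
- **Known risk bands.** The abbreviation list has "PDVHR: Postpartum Depression Very High Risk" beside a high-risk label. Neither is used in the visible text or tied to EPDS scores, and they may belong to the figure that is not shown.
- **No effect estimate at all.** Confidence intervals are promised, and ANCOVA supplies an estimate on the score. What can be said is that no effect measure is named for the categories. Leaving such detail, and the exact cut-offs, to a fuller plan is normal for an article; the choice of chi-square is stated.

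**Conclusion.** The point holds, conditionally and with limited reach. The article fixes a test that ignores order for the between-arm comparison of a variable that it models as ordinal a few lines later, in a model that does not name arm. If the category has three or more levels, the chi-square test at 30 per arm gives up roughly 7 to 11 points of power with three bands (up to about 13 in some assumed scenarios) and about 11 to 19 with four, and its result has no direction. With two levels there is no loss.

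The sizes assume two-sided 5% tests, an SD of about 6.5 where scores are simulated with the 5.5-point effect (4 to 5 in the variants), assumed control shares or means, and either proportional odds or a normal shift. The trial's main inference on the EPDS score is not affected. The change is worth making because it is cheap and removes an internal inconsistency.

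**What to change.** In Data processing, restrict the chi-square test to two-level EPDS splits and add wording such as: for any EPDS category with three or more ordered levels, the arms will be compared by ordinal regression with treatment arm and baseline EPDS as independent variables, analysed as randomised, and the common odds ratio will be reported with its 95% confidence interval.

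This extends a model class that the plan already intends to fit in its named software, and baseline EPDS is already collected. It gives one estimate, one interval and one p-value from the same model, and meets the promise of confidence intervals for this comparison.

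The cost is one or two sentences, with no new data, visits or patients. There are two small downsides:

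- **Proportional odds.** The model assumes that the treatment odds ratio is the same at every cut. Ordinal regression as usually fitted already makes this assumption for its predictors.
- **Sparse bands.** Estimates may be unstable. In simulated tables with control means of 7 to 9 and SD 4 to 5, 58–100% had an expected count below 5. A linear-by-linear trend test can serve as a sensitivity analysis, with the sparseness threshold for using it set before the data are seen. It should not replace the model's p-value after the fact, because an unadjusted test and an adjusted odds ratio can disagree.
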